**Abstract:**

Gastroparesis (GP), defined as delayed gastric emptying without any mechanical obstruction affects up to 10 million individuals in the United States. Improvement of symptoms is achieved in up to 50-60% of drug refractory patients treated with gastric electrical stimulation (GES), but this therapy has minimal or no effect on the acceleration of gastric emptying (GE). To address this therapeutic deficiency, we have added surgical pyloroplasty (PP) as a supplementary procedure to accelerate GE in drug refractory gastroparetics undergoing implantation of GES. Based on our experience, there was more than 70% improvement in total GP symptom scores (TSS) in the follow-up evaluation and GE was normalized in 60 % of GP patients who received combined GES and pyloroplasty, suggesting that the combination of PP and GES significantly accelerate gastric emptying and improve GP symptoms exceeding the results previously achieved by GES alone. Now, the question is whether pyloroplasty alone could be sufficient for the achievement of both subjective and objective goals of improvement in drug refractory gastroparesis. Therefore, in the current proposal, we plan to compare TSS outcome, quality of life and GE in drug refractory GP patients who will receive both GES implantation and PP during the surgery and then are evaluated during a GES-off or –On period based on a randomized double blind study design. As a secondary goal, we will also examine whether the baseline pyloric and antral interstitial cells of Cajal (ICC) counts as well as the presence of pyloric fibrosis could predict clinical response to PP.

42  
43  
44  
45 **Research Plan: A) Specific Aims**

46 **1)** To assess the effects of gastric electrical stimulation (GES) and pyloroplasty on total GP  
47 symptoms scores (TSS) and quality of life in drug refractory gastroparetic patients during GES -  
48 ON and GES -OFF periods.

49 **2)** To assess the effects of gastric electrical stimulation (GES) and pyloroplasty on gastric  
50 emptying of a radiolabeled marker in drug refractory gastroparetic patients during GES-ON and  
51 GES -OFF periods.

52 **3)** To understand whether pyloroplasty alone is effective for achieving both subjective and  
53 objective goals of improvement in drug refractory gastroparesis.

54 **4)** To understand whether the status of antral and pyloric ICC counts and/or the presence of  
55 pyloric fibrosis predicts the clinical outcome.

56  

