57 **B) Background/significance:**  
58

59 Gastroparesis (GP), affecting up to 10 million individuals in the United States, is a relatively  
60 common gastrointestinal (GI) motility disorder and is defined as delayed gastric emptying without  
61 any mechanical obstruction. Gastroparesis presents with upper GI symptoms such as nausea,  
62 vomiting, bloating, postprandial fullness, early satiety and abdominal pain. The etiology of  
63 gastroparesis is not well recognized and the majority of cases are idiopathic (ID-GP), while many  
64 others are diabetic (DM-GP). Patients with gastroparesis suffer from nutritional deficiencies and  
65 metabolic consequences as well as impaired social activities and quality of life. Treatment of  
66 gastroparesis is based on alleviating symptoms, correcting nutritional abnormalities and targeting  
67 the underlying causes, although it is usually challenging and often disappointing . Therefore,  
68 studying the treatment options of this debilitating disorder are among the priorities in the field of GI  
69 motility disorders.

70  
71  
72 Clinically gastroparesis is categorized as mild, moderate and severe. Mild gastroparesis presents  
73 with occasional symptoms which do not have a significant impact on work and family functioning.  
74 The treatment in this group is based on diet modification, antiemetics and glucose control.  
75 Moderate gastroparesis presents with daily but not continuous symptoms and occasional  
76 hospitalization, interfering with work and family functioning. Diet modifications, prokinetics, one or  
77 more antiemetics and glucose control as well as addressing pain and psychological aspects are

recommended in these patients. In severe Gastroparesis daily continuous symptoms are present resulting in multiple hospitalizations and inability to work and function. Severe gastroparesis is treated with combining prokinetics, multiple antiemetics and nutrition enteral support. Up to 30% of gastroparetic patients fail current medical therapy and need surgery including gastric electrical stimulation (GES) implantation and/or pyloroplasty as the next step.

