### Inclusion criteria:

Documented diagnosis of GP for > 1 year and refractoriness to anti-emetics and prokinetics; more than 7 emetic episodes per week; and delayed GE (gastric retention greater than 60% at 2 h and/or greater than 10% at 4 h) based on a 4-h standardized radionuclide solid meal test.

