### Exclusion Criteria:

Organic or pseudo-obstruction, primary eating or swallowing disorders, positive pregnancy test result, psychogenic vomiting, peritoneal dialysis, drug dependent, morbid obesity, active malignancy and whoever received PP or GES in the past.

**D2) Sample Size:** As this study is designed to conclude that pyloroplasty is not inferior to GES plus pyloroplasty, the sample size for the non-inferiority trial by including % normalization of the GE as the binary outcome is calculated based on: "Blackwelder WC."Proving the Null Hypothesis" in Clinical Trials. Control. Clin. Trials 1982; 3:345-353." GE was normalized in 60 % of GP patients with GES-ON

plus Pyloroplasty based on our preliminary data. On the other hand, based on our patients' database, GES alone normalizes GE in around 18% of GP patients, predominantly in idiopathic GP. By defining non-inferiority limit equal to  $(60 - 18 = 42\%)$ , and percentage of success in the GES-ON plus pyloroplasty group, 17 patients will be included in each arm of this study. Therefore, this study is designed to include overall 34 drug-refractory GP patients who will undergo surgery for GES implantation plus pyloroplasty. Based on our records, we have at least 2 surgeries per month; therefore, we predict that it takes approximately 1.5 years to recruit all patients.

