**D3) Study Design:** After receiving IRB approval, the patients will be screened and the project will be discussed with the potential candidates for GES implantation plus pyloroplasty. Based on the inclusion/exclusion criteria, the baseline gastric emptying test (GET) based on the 4-h standardized radionuclide solid meal protocol will be performed and 34 patients will be included in the study. Our effort would be to include similar numbers of idiopathic and diabetic patients in each intervention group based on a block randomization method. The patients will be followed up for 1 month, while their PAGI-SYM, PAGI-QOL and TSS severity/frequency will be recorded on a Standardized Symptoms Interview Form, which assesses the symptoms of gastroparesis occurring during the last 2 weeks before the interview for severity of vomiting, nausea, early satiety, bloating, postprandial fullness, and epigastric pain. The severity of each symptom will be graded by the patients as 0=absent, 1=mild (not influencing usual activities), 2=moderate (diverting from, but not urging modifications, of usual activities), 3=severe (influencing usual activities, severely enough to urge modifications), and 4=extremely severe (requiring bedrest). The sum of the severity ratings of the six symptom subscores comprises the overall total symptom score (TSS) in severity.

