PAGI-SYM and TSS questionnaires will be filled every 2 weeks during the study period. GES implantation together with the Heineke-Mikulicz PP will be performed laparoscopically (<10% of cases may require open approach). Only one surgeon using the same technique at all times will perform the surgeries. In GES-ON group, GES will be turned on immediately after the operation. On the other hand, in GES-OFF group, the GES will remain OFF for the first 3 months, while symptoms will be recorded again in both groups. After 3 months, follow up GET will be performed and in GES-OFF group, the device will be turned ON. Both groups will be followed for 3 more months clinically, to record any possible changes in their symptoms. Moreover, 36-Item Short Form Health Survey (SF-36), Beck depression inventory (BDI), State-trait anxiety inventory (STAI) and the patient health questionnaire (PHQ-15) will be completed at baseline followed by 3 and 6 months after the surgery. The amount of anti-emetics and prokinetics, days of hospitalization and ED visits and any possible complication will be recorded during the study period. Glucose control in diabetic patients will be monitored by HbA1c. Pain will also be monitored regarding narcotic need. During the follow-up patients will be instructed to remain on a mechanical soft diet of smaller meals, low fat, and low fiber. Evaluators of clinical outcome, the radiologist and the biostatistics consultant as well as the patient will remain blind to the GES-ON or -OFF status before the results get finalized. The individual programming the device will have no clinical rule to avoid any bias.

One of our Investigators, [name] is assigned to serve as an un-blind person, who is going to generate a master list of participants by dividing them into two groups based on their etiologies (diabetic or idiopathic). All efforts would be to include similar numbers of idiopathic and diabetic patients in each intervention group based on a block randomization method, allowing for GES to be turned ON at the surgery, or it will stay OFF for the 3-month-long blind portion of the study.

The following flow-diagram summarizes the steps of this study:

[figure not shown]

Early termination of the study will occur if a patient decides not to continue the study or if in the GES-OFF group, the nausea/vomiting symptoms are not manageable after 6 weeks of the operation, which is the usual time for surgical healing.

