**Histological evaluation of the biopsy samples:** Paraffin embedded formalin fixed tissues will be cut at 3-4 microns thick and mounted on slides containing paired sections from cases and controls. Subsequently, the tissues will be deparaffinized and immunostained by BenchMark XT automated staining instrument. Briefly, the slides will through peroxidase block and antigen retrieval solutions before applying the primary antibodies (C-Kit clone YR145 from Cellmark, Rocklin, CA). Then, the slides will be washed and incubated with the secondary antibody followed by horseradish peroxidase (HPR). At the end, Chromogen will be added and the slides will be counter-stained by Hematoxylin. Pathology slides will be read by a pathologist who will be blind to the diagnosis of the patients, ICC will be counted per high power field (HPF) and the mean of ICC from examining 20 HPF will be calculated. For collagen fibrosis, the biopsies will be stained with trichome. Presence of diffusely distributed collagen between single muscle fibers will be defined as fibrosis and graded as mild, moderate and severe.

**Gastric emptying test:** Gastric emptying test will be performed utilizing a standardized meal consisting of egg beaters labeled with 99m technetium sulfur colloid accompanied by 2 toasts with strawberry jelly and 120 cc of water will be given to the patients (total calories- 240 and 2% fat). Anterior and posterior images will be obtained in the standing position immediately after meal ingestion and at 30 minutes, 1, 2, 3 and 4 hours. Geometric mean calculation and decay correction will be performed on all images. The radiologist will also be blind to the treatment groups.

The radiation exposure of a gastric emptying is equivalent to a chest x-ray or flying across country on an airline. Therefore, this test can be justified for repeating in 3 months.

**D4) Statistical analysis:** In the current study, the following parameters will be analyzed:

- 1) Changes of total gastroparesis symptom scores (TSS) and gastric retention of the radiolabeled meal (%) at 2-4 hrs in each group. TSS will include both severity and frequency.
- 2) Total Symptom Score (TSS) with severity and frequency of gastroparesis symptoms in each etiological subgroup of patients if enough study power would be achieved.
- 3) Associations between changes in gastric emptying and TSS.
- 4) Associations between changes in gastric emptying and ICC count/ pyloric fibrosis.

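### Aim 3 asks whether pyloroplasty alone is effective, but every patient has pyloroplasty and only GES ON versus OFF is randomised, so the trial cannot attribute improvement to pyloroplasty

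*Protocol*

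**What the plan says.** Section A, aim 3, is "To understand whether pyloroplasty alone is effective for achieving both subjective and" objective goals in drug-refractory gastroparesis.

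The design is in D2 and D3. D2 says "this study is designed to include overall 34 drug-refractory GP patients who will undergo surgery for GES implantation plus pyloroplasty", so no patient goes without pyloroplasty. D3 describes block randomisation within etiology, "allowing for GES to be turned ON at the surgery, or it will stay OFF for the 3-month-long blind portion of the study". Patients, outcome evaluators and the radiologist are blind to device state.

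D4 item 1 lists, among the parameters to be analysed, "Changes of total gastroparesis symptom scores (TSS) and gastric retention of the radiolabeled meal (%) at 2-4 hrs in each group". The rest of D4 provides for comparing baseline with follow-up values and for time trends by repeated-measures ANOVA or Friedman test.

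Elsewhere the question is narrower. The bold question in section B is whether pyloroplasty without GES could do as well as the combination. D2 sizes the trial to show that pyloroplasty is not inferior to GES plus pyloroplasty on normalisation of emptying, with 17 per arm and a margin of 60 - 18 = 42 percentage points.

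**The concern.** An aim that asks whether a procedure is effective needs a comparison with patients who did not have it, or a stated substitute for that comparison. This trial has no such concurrent group. The aim can be approached in two ways, and neither isolates pyloroplasty: the randomised ON-versus-OFF contrast holds pyloroplasty constant, and the before-after change in the OFF arm has no control.

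If the OFF arm improves markedly, Aim 3 as worded invites the conclusion that pyloroplasty alone works. The same data could arise if much of the improvement came from something else common to both arms. What is at stake is an efficacy claim for a surgical procedure. The validity of the randomised comparison is not in question.

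**Working it through.** **1. What the randomised contrast estimates.** Write the mean outcome in the ON arm as pyloroplasty + GES + shared influences, and in the OFF arm as pyloroplasty + shared influences (effects taken as additive, for illustration). The difference is the GES term. Pyloroplasty cancels, and so do the shared influences.

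**2. The plan's sample size belongs to that contrast.** Inputs from D2: 60% normalisation in both arms, margin 0.42. D2 does not state alpha or power; one-sided 0.05 and 80% power are assumed because they reproduce the figure:

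n = (1.645 + 0.842)² × (0.6 × 0.4 + 0.6 × 0.4) / 0.42² = 6.18 × 0.48 / 0.1764 ≈ 16.8, rounded up to 17 per arm.

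This reproduces the stated 17. It concerns ON versus OFF only.

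**3. Non-inferiority does not imply that pyloroplasty worked.** Suppose 3 of 17 (17.6%) normalise in each arm, about the 18% that D2 gives for GES alone. The difference is 0, with standard error √(2 × 0.176 × 0.824 / 17) ≈ 0.131. The one-sided 95% lower limit is -1.645 × 0.131 ≈ -0.22, inside the margin of -0.42. Non-inferiority would be declared although neither arm did better than the protocol's own rate without pyloroplasty. (The normal approximation is rough at these counts, but the distance from the margin is wide.)

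**4. What the OFF-arm change contains besides pyloroplasty.**
- Expectation: patients know they had an operation and, being blind to device state, may believe that the device is active (D3).
- Selection: entry requires "more than 7 emetic episodes per week" and delayed emptying above set limits (Inclusion criteria).
- Diet: D3 says "During the follow-up patients will be instructed to remain on a mechanical soft diet of smaller meals, low fat, and low fiber".
- Medication: amounts of anti-emetics and prokinetics are recorded in D3, and section B counts changes in them among the outcomes, so they may vary.

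No concurrent group without pyloroplasty separates these from the procedure.

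**5. How far TSS falls without pyloroplasty in the protocol's own data.** D3 defines severity TSS as the sum of six items; epigastric burning is not one of them.

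| Series | Baseline, six items | Follow-up, six items | Fall |
|---|---|---|---|
| GES only (Table 2) | 3.5+3+2.9+2.8+2.8+2.5 = 17.5 | 1.6+1.4+1.5+1.4+1.4+1.3 = 8.6 | 8.9/17.5 = 51% |
| GES + pyloroplasty (Table 1) | 3.6+3.2+3.2+2.5+2.8+2.7 = 18.0 | 1.1+0.6+0.9+0.9+1.0+1.0 = 5.5 | 12.5/18.0 = 69% |

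The text of C2 gives about 48% for GES only; the difference from 51% does not affect the argument. GES was on in that series, so 51% is not a placebo estimate. It shows only that a fall of about half is seen without pyloroplasty.

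**6. Emptying.** C2 reports no significant change in mean emptying with GES only, and D2 gives 18% normalisation, against 60% in the combined pilot. A large change in retention in the OFF arm would therefore be harder to explain without pyloroplasty than a large change in TSS.

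**The case against.** The strongest reply is that Aim 3 should be read in context. Section B and D2 ask whether pyloroplasty with the device off does as well as pyloroplasty with the device on, and the randomised contrast addresses that. D4 item 1 is one entry in a list of parameters. Nothing ties it to Aim 3 or makes it a within-arm efficacy test, and D4 also names two-sample tests. This stands. It also shows the remedy, since the aim needs only to be worded as those sections word it. As written, it asks about effectiveness, which is a different question.

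A second reply is that the margin brings in a reference without pyloroplasty, namely 18% normalisation with GES alone. That is a fair point for emptying. The reference is nevertheless historical: it comes from the site's database, and the GES-only series in C2 had at least 1 year of follow-up and included 31 postsurgical cases. Any inference from it is indirect and should be labelled so.

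A third reply is that some of the shared influences may be small. TSS is not an entry criterion, so selection acts on it only indirectly, through vomiting and refractoriness. The diet instruction speaks of remaining on the diet, so it may not be new. In section B, the sentence "The treatment in this group is based on diet modification, antiemetics and glucose control" concerns mild disease; diet is also listed for moderate disease but not in the sentence on severe disease. These points stand. They limit what can be said about size, but they do not supply the missing comparison.

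**Conclusion.** The point holds as a mismatch between Aim 3 and the design. With pyloroplasty in all 34 patients, neither ON-versus-OFF non-inferiority nor the OFF-arm change from baseline can attribute improvement to pyloroplasty. This follows from the design and needs no numerical assumption. For scale, the protocol's own series without pyloroplasty shows a 51% fall in six-item TSS, so a fall of that order in the OFF arm would not be specific. For emptying the concern is weaker, for the reasons given above.

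A reader might infer more than this, and the documents do not support it:
- That regression to the mean explains the OFF-arm change. The protocol gives no retest reliability, so its size cannot be derived, and the GES-only emptying data argue against it as the sole explanation of a large emptying change.
- That the qualifying emptying test is certainly the baseline. D3 says "Based on the inclusion/exclusion criteria, the baseline gastric emptying test (GET) based on the 4-h standardized radionuclide solid meal protocol will be performed", which suggests this but does not settle it.
- That the OFF-arm change is the only planned route to the question, or that the sponsor will report it as proof of efficacy. Section B and D2 give the randomised reading, and D4 states no such conclusion.
- That the trial as a whole fails. The randomised question about GES is unaffected by this point.

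**What to change.** Restate Aim 3, and the conclusion to be drawn from it, to match section B and D2: whether GES OFF plus pyloroplasty gives results similar to GES ON plus pyloroplasty through 3 months, in patients who all had pyloroplasty.

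In D4, state that the change from baseline in the GES-OFF arm is descriptive. Alternatively, present it as an explicitly indirect comparison with the historical GES-only data, naming the differences in period, follow-up and case mix. In either case make no causal claim of pyloroplasty efficacy.

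Optionally, define baseline TSS as the mean of the pre-operative scores already planned: those from the baseline period and the day of surgery in section B and, if it precedes the operation as the order of D3 suggests, the 1-month follow-up.

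The cost is wording only, with no new arm, patient, visit or measurement. The downside is that the sponsor gives up a claim of efficacy for pyloroplasty alone, which the design cannot support.

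### The outcome on which the trial is sized, GE normalisation against a 42-point margin, does not appear in the D4 analysis list, and D4 does not say which of its listed outcomes decides the conclusion

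*Protocol*

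**What the plan says.** **D2 (sample size)** states that the study aims to show pyloroplasty alone is not inferior to GES plus pyloroplasty, and calculates "the sample size for the non-inferiority trial by including % normalization of the GE as the binary outcome". It takes 60% as the rate with GES-ON plus pyloroplasty, subtracts the 18% it gives for GES alone to obtain a 42-point limit, and arrives at 17 per arm. It states no alpha and no power.

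**D4 (statistical analysis)** lists six items.
- Item 1 is "Changes of total gastroparesis symptom scores (TSS) and gastric retention of the radiolabeled meal (%) at 2-4 hrs in each group", and it adds that "TSS will include both severity and frequency".
- Items 2 to 5 are subgroup TSS and associations among emptying, TSS, interstitial cell counts and fibrosis.
- Item 6 relates questionnaire scores and HbA1c to treatment. After Amendment 2 removed the BDI and STAI, this leaves SF-36, PHQ-15 and HbA1c.

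The methods named are t-test or Mann-Whitney, repeated-measures ANOVA or Friedman, and Pearson or Spearman correlation.

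**The abstract** says "we plan to compare TSS outcome, quality of life and GE in drug refractory GP patients". Aim 1 concerns TSS and quality of life, and Aim 2 concerns emptying. Aim 3 begins "To understand whether pyloroplasty alone is effective for achieving both subjective and" and goes on to objective goals. The one explicit ranking is the abstract's label of the cell-count and fibrosis work as a secondary goal.

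**The concern.** The design section and the analysis section describe different trials. D2 asks whether a difference in two proportions stays within a margin. D4 asks whether continuous or ordinal scores differ. An analyst working from D4 would never produce the result that justified 17 per arm.

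That leaves the central question, whether pyloroplasty alone suffices, to be answered from TSS severity, TSS frequency, retention or a questionnaire, with no order among them. Two errors become possible. One significant result among several could be presented as proof that GES is needed. Or a non-significant difference in a small trial could be presented as proof that GES is not needed, although no margin exists for any outcome other than GE normalisation.

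**Working it through.** **1. Reproduce the plan's figure.** The inputs from D2 are p = 0.60 in both arms ("GE was normalized in 60 % of GP patients with GES-ON" plus pyloroplasty) and margin 0.60 − 0.18 = 0.42 ("GES alone normalizes GE in around 18% of GP patients, predominantly in idiopathic GP"). Alpha and power are not stated.

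n per arm = (z₁₋α + z₁₋β)² × 2p(1 − p) / margin²

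- One-sided 5%, 80% power: (1.645 + 0.842)² × 0.48 / 0.1764 = 16.8, so 17. This matches.
- One-sided 2.5%, 80% power: 21.4, so 22. With 17 per arm the power at this level is 70.5%.

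Of the usual alpha and power combinations tried, only one-sided 5% with 80% power gives exactly 17. The sample size therefore belongs to the GE normalisation comparison.

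**2. Look for that comparison in D4.**

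| Element of the D2 question | In D4? |
|---|---|
| Proportion with normalised GE | No; only % retention at 2-4 h |
| Method for a difference in proportions | No |
| 42-point margin | No |
| Statement of which outcome decides | No |

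**3. What the missing analysis would look like.** With 10/17 normalised on GES-ON and 8/17 on GES-OFF, the difference is −2/17 = −11.8 points. The standard error is √[(0.2422 + 0.2491)/17] = 0.170. The one-sided 95% lower limit is −0.118 − 1.645 × 0.170 = −0.397, inside −0.42, so non-inferiority would be met. With 7/17 the limit is −0.454 and it would not. No method listed in D4 yields this result.

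**4. Why a non-significant difference is not a substitute.** With 17 per arm, the TSS difference detectable with 80% power at two-sided 5% (assumed) is (1.960 + 0.842) × √(2/17) = 0.96 SD. A true difference of 0.5 SD would be detected only about 30% of the time, so a non-significant TSS result does not show adequacy.

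**5. Illustration of unranked difference tests.** Assume 0.05 per test and that any one significant result counts. Under independence the rate is 1 − 0.95ᵏ; the correlated values come from simulated, equally correlated normal statistics, two-sided.

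| Tests | Independent | Correlation 0.5 | Correlation 0.9 |
|---|---|---|---|
| 3 | 14.3% | 12.5% | 8.4% |
| 4 | 18.5% | 15.6% | 9.4% |

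The range is 8.4/5 = 1.7 to 18.5/5 = 3.7 times nominal.

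**The case against.** The strongest reply is that the deciding comparison is already there. D2 gives the contrast, hypothesis, outcome and margin. D3 schedules a single follow-up emptying test, at 3 months, after which the GES-OFF arm is switched on, so the time point follows too. Alpha, testing order and exploratory labels are commonly left to a statistical analysis plan, which may exist.

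Much of this stands. A reader might infer that the protocol has no deciding comparison at all; D2 does not support that. The absence of a multiplicity scheme is not a defect by itself. What the reply does not answer is the mismatch inside the document. D4 lists its parameters and tests, and the D2 outcome and margin are not among them, so an analysis plan written from this protocol would have to choose between D2 and D4.

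Two further inferences are tempting and go too far.
- *The trial has a threefold false-positive rate.* The protocol states no alpha, number of decisive tests or any-one-counts rule. Item 1 speaks of changes within each group, so even the number of between-arm tests is an inference. The rate also concerns claims that GES matters, not the non-inferiority claim.
- *Emptying and symptoms will point opposite ways in a quarter to two-thirds of trials.* That needs assumed TSS effects of 0.5 to 1.0 SD and independent endpoints. The roughly 48% TSS improvement in C2 is an uncontrolled before-after change without pyloroplasty. It does not estimate what GES-ON adds over GES-OFF after pyloroplasty. Naming a primary outcome would not change such discordance anyway.

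**Conclusion.** The point holds as a mismatch between D2 and D4. The study is designed and sized on GE normalisation with a 42-point margin, and D4 neither lists that outcome nor tests it against the margin. No outcome is designated primary, and the abstract and aims set TSS, quality of life and emptying side by side. This conclusion rests on the text and needs no assumption.

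The size of the consequence cannot be fixed from the protocol. The 8% to 19% range is an illustration under an assumed 0.05 per test and an any-one-counts rule. For a claim of non-inferiority on TSS, quality of life or retention, no error rate can be given, because no margin is set. The 42-point margin is taken as given here; whether it is defensible is a separate question.

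**What to change.** In D2 and D4:
- Designate GE normalisation at the 3-month emptying test, GES-OFF versus GES-ON, as the single primary comparison.
- State the alpha and power. One-sided 5% with 80% power is what reproduces 17 per arm.
- Add to D4 the confidence interval for the difference in proportions, to be compared with the D2 margin.
- Name change in TSS severity at 3 months as key secondary, reported with its 95% CI.
- State that a result on GE alone supports a claim about emptying only. Aim 3 covers subjective as well as objective goals, and the protocol itself says GES has little or no effect on emptying. A rule that blocks the wider claim only when TSS significantly favours GES-ON would not be enough, for the reason in step 4 of the working.
- Label TSS frequency, 2-h and 4-h retention, SF-36, PHQ-15, HbA1c and all 6-month comparisons exploratory. At 6 months both arms have the device on, so those data no longer compare ON with OFF.

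The cost is a few sentences, with no added patients, visits or tests. The downside is that results other than the primary can be reported only as supportive.
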